**Implementation**			
	mHealth^e^ intervention acceptability (from TFA^f^)	Individual participant (client or potential PrEP user)	Survey of all participants receiving mHealth intervention immediately upon the completion of SOC^g^ or SOC and mHealth education and counseling Qualitative interview (12 participants per site who receive mHealth and SOC) during the enrollment period for step 1
	mHealth intervention effectiveness (from RE-AIM^h^)	Individual participant (client or potential PrEP user)	Knowledge survey of all participants receiving mHealth intervention immediately upon the completion of SOC or SOC and mHealth education and counseling Qualitative interviews of 8 participants per site who receive SOC counseling and 12 participants who receive SOC and mHealth education and counseling about their knowledge and beliefs about oral and CAB-LA PrEP in relation to their choice Adherence data at the end of the study
	mHealth tool acceptability (TFA) and feasibility (from Proctor et al [31])	Individual provider and clinic setting	Interviews at the end of the study including questions that will generate both qualitative and quantitative data
	WhatsApp appointment reminder acceptability (TFA)	Individual client or PrEP user	Brief survey given to each participant who received WhatsApp appointment reminders at their month 5 visit Qualitative interviews (16 participants per site) conducted at month 7
	WhatsApp appointment reminder effectiveness (from RE-AIM)	Individual client or PrEP user	Study adherence data at the middle and end of the study Qualitative interviews (16 participants per site) conducted at month 7
	WhatsApp appointment reminder feasibility (Proctor et al [31]) and implementation (RE-AIM)	Individual provider and clinic setting	Interviews at the end of the study including questions that will generate both qualitative and quantitative data WhatsApp appointment reminder program data files
	Acceptability (TFA) of STI^i^ self-test	Individual client or CAB-LA PrEP user	Qualitative interviews (16 participants per site) conducted at month 7
	Acceptability (TFA) and feasibility (Proctor) of STI self-test	Individual provider and clinic setting	Qualitative interviews at the end of the study
	Acceptability (TFA) of HIV self-testing	Individual client or CAB- LA PrEP user	Qualitative interviews (16 participants per site) conducted at month 7
	Implementation: barriers to and facilitators of the integrated delivery of CAB-LA PrEP in the existing oral PrEP services	Individual participant (client or CAB-LA PrEP user) Individual provider and clinic setting	Qualitative interviews (16 participants per site) conducted at month 7 Interviews at the end of the study including questions that will generate both qualitative and quantitative data
	Feasibility of CAB-LA PrEP in public clinic PrEP services	Individual provider and clinic setting	Interviews at the end of the study including questions that will generate both qualitative and quantitative data Review of routine study documentation
	Maintenance	Individual participant (client or CAB-LA PrEP user)	Adherence to injection visits at the middle and end of the study
	Reach	Individual participant and cohort characteristics	Survey of all participants receiving mHealth intervention immediately upon the completion of SOC or SOC and mHealth education and counseling about the rationale for their PrEP choice Qualitative interview (12 participants per site who receive mHealth and SOC) during the enrollment period for step 1 that will include questions about the rational for their PrEP choice Study data on the number of participants enrolled and pace of enrollment and demographic data

^a^CAB-LA: long-acting injectable cabotegravir.

^b^TDF: tenofovir disoproxil fumarate.

^c^FTC: emtricitabine.

^d^PrEP: preexposure prophylaxis.

^e^mHealth: mobile health.

^f^TFA: theoretical framework for acceptability.

^g^SOC: standard of care.

^h^RE-AIM: Reach, Effectiveness, Adoption, Implementation, and Maintenance.

^i^STI: sexually transmitted infection.

### Statistical Analysis

Our major clinical outcome (primary analysis) will adopt an intent-to-treat approach and compare HIV incidence (and 95% CI) among individuals in the CAB-LA cohort with HIV incidence (and 95% CI) among individuals on daily PrEP within the Brazilian SUS. We will estimate the rate of HIV incidence with 95% CI in each group using Kaplan-Maier statistics. We will use a Cox proportional hazard model to assess the relative hazard (hazard ratio with 95% CI) between the 2 groups, overall and by site, age category, and gender.

It is anticipated that there will be an average follow-up of 1.5 years per person with at least 75% retention each year (N=1350 person-years of follow-up) and that incidence will be higher than that observed in HPTN 083 in Latin America (0.60 per 100 person-years). If the observed incidence is approximately 50% higher than that observed in HPTN 083, the study will be able to estimate an incidence of 0.85 (95% CI of 0.47-1.42) per 100 person-years (Table 6). If the observed incidence is approximately twice as high as that observed in HPTN 083, then the study will be able to estimate an incidence of 1.18 (95% CI of 0.72-1.82) per 100 person-years. If the comparison group is of similar size, then the incidence would need to be 2.2 to 2.5 times higher to observe statistically significant differences between CAB-LA and oral PrEP. However, if the comparison group is 3 times larger, then the incidence would need to be 2 to 2.2 times higher to observe statistically significant differences between CAB-LA and oral PrEP.

To reach the primary implementation objective, we will report descriptive statistics (numbers, proportions, and medians) of Likert-scale responses to the TFA constructs (affective attitude, burden, ethicality, intervention coherence, opportunity costs, and perceived effectiveness and self-efficacy) among health care providers.

**Table 6 table6:** Observable differences given potential HIV incidence in intervention and comparison groups.

Group				Incidence (95% CI)

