**Methods:**

This type-2 hybrid implementation-effectiveness study includes formative work, qualitative assessments, and clinical steps 1 to 4. For formative work, we will use participatory design methods to develop an initial CAB-LA implementation package and process mapping at each site to facilitate optimal client flow. SGMs aged 18 to 30 years arriving at a study clinic interested in PrEP (naive) will be invited for step 1. Individuals who tested HIV negative will receive mHealth intervention and standard of care (SOC) counseling or SOC for PrEP choice (oral or CAB-LA). Participants interested in CAB-LA will be invited for step 2, and those with undetectable HIV viral load will receive same-day CAB-LA injection and will be randomized to receive digital appointment reminders or SOC. Clinical appointments and CAB-LA injection are scheduled after 1 month and every 2 months thereafter (25-month follow-up). Participants will be invited to a 1-year follow-up to step 3 if they decide to change to oral PrEP or discontinue CAB-LA and to step 4 if diagnosed with HIV during the study. Outcomes of interest include PrEP acceptability, choice, effectiveness, implementation, and feasibility. HIV incidence in the CAB-LA cohort (n=1200) will be compared with that in a similar oral PrEP cohort from the public health system. The effectiveness of the mHealth and digital interventions will be assessed using interrupted time series analysis and logistic mixed models, respectively.

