#### Step 1: mHealth Intervention

##### Overview

Step 1 focuses on evaluating the mHealth intervention and participants’ choice of PrEP method (Table 1). Potential step 1 participants include individuals who come to a study clinic looking for PrEP, are PrEP naive, and have expressed an interest in taking PrEP (see eligibility criteria). All individuals accessing the service for PrEP will be assessed for study eligibility by a designated study staff member. Eligible participants will be asked whether they are interested to assess educational and counseling interventions for PrEP choice.

After signing step 1 informed consent, participants will undergo rapid tests for HIV, syphilis, and hepatitis B and C. Rectal, oral, and urine swab samples will be collected for *Chlamydia trachomatis* and *Neisseria gonorrhoeae* nucleic acid amplification testing. If a reactive or positive result is obtained for HIV test, the respective person is deemed ineligible to receive PrEP. Additional testing to confirm suspected HIV infection will be performed in accordance with local guidelines. If an HIV infection is confirmed, the participants will receive counseling and be immediately referred for HIV treatment and care. All participants will be evaluated for signs or symptoms of a possible acute HIV infection. Those with suspected acute HIV infection will be referred for follow-up investigation within the public health system.

Participants at each site will receive counseling and education on the use of PrEP options per the local SOC from a health care provider until 100 participants indicate that they would like to start CAB-LA PrEP and enroll in step 2. Additional participants will receive an mHealth education and counseling intervention plus the SOC education and counseling until 100 participants exposed to both SOC and the mHealth intervention enroll in step 2 of the study at each site (200 participants enrolled per site).

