**Intervention: CAB-LA^a^ **PrEP**^b^**				
	**1350 py^c^ incidence/100 py**			
		8 cases	0.59 (0.28-1.13)	
		12 cases	0.89 (0.48-1.51)	
		18 cases	1.19 (0.71-1.88)	

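### The per-group HIV incidence rate is assigned to Kaplan-Meier, which gives a cumulative probability, while the benchmark, precision statements and Table 6 are all per 100 person-years

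*Protocol article*

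**What the plan says.** The Statistical Analysis section of the protocol article names the estimator of the primary clinical outcome in one sentence: "We will estimate the rate of HIV incidence with 95% CI in each group using Kaplan-Maier statistics". The next sentence plans a Cox model for the hazard ratio "between the 2 groups, overall and by site, age category, and gender".

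The planning text in the same section is on another scale. It assumes "average follow-up of 1.5 years per person with at least 75% retention each year (N=1350 person-years of follow-up", takes 0.60 per 100 person-years from HPTN 083 in Latin America as the benchmark, and promises precision of 0.85 (0.47-1.42) and 1.18 (0.72-1.82) per 100 person-years. Table 6 lists case counts, person-years and rates. Its CAB-LA block is labelled "1350 py^c^ incidence/100 py" and shows 8, 12 and 18 cases.

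The CAB-LA cohort has 1200 people in six cities, and the Step 1 overview sets "200 participants enrolled per site".

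**The concern.** A Kaplan-Meier estimate is a percentage infected by time t, and it grows with t. A rate per 100 person-years does not depend on the length of follow-up when the hazard is constant. The analysis sentence asks for the second and names the method for the first, without giving a time point. Follow-up lasts between 1 and 2 years (Specific Visit Procedures), and the visit schedule runs to month 25 (Table 2), so the choice of time point changes the answer.

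At stake is the per-group result of the primary outcome. If the sentence is followed literally, that result need not be comparable with the benchmark or with the intervals in Table 6.

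A smaller question is what the by-site hazard ratios could show, given how few CAB-LA infections are planned for.

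**Working it through.** **Inputs.** From Statistical Analysis: 1.5 years average follow-up, 75% retention, 1350 person-years. From the abstract: n=1200. From Table 6: CAB-LA cases of 8, 12 and 18; oral PrEP cases of 24, 30 and 36 on 1350 person-years. From Study Design: six sites. Assumptions, not in the article: constant hazard, equal sites, and comparator person-time spread over sites in proportion.

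**1. The plan's own figures.** Person-years: 1200 × 1.5 × 0.75 = 1350, as printed. Rate = cases / person-years × 100. The mid-P Poisson limits for x cases are the expected counts L and U that solve P(X > x | L) + 0.5·P(X = x | L) = 0.025 and P(X < x | U) + 0.5·P(X = x | U) = 0.025, each divided by person-years.

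| Cases / person-years | Table 6 | mid-P | exact Poisson |
|---|---|---|---|
| 8 / 1350 | 0.59 (0.28-1.13) | 0.59 (0.28-1.13) | 0.59 (0.26-1.17) |
| 12 / 1350 | 0.89 (0.48-1.51) | 0.89 (0.48-1.51) | 0.89 (0.46-1.55) |
| 18 / 1350 | 1.19 (0.71-1.88) | 1.33 (0.82-2.07) | 1.33 (0.79-2.11) |
| 36 / 1350 | 2.67 (1.90-3.65) | 2.67 (1.90-3.65) | 2.67 (1.87-3.69) |
| 94 / 4050 | 2.32 (1.89-2.83) | 2.32 (1.89-2.83) | 2.32 (1.88-2.84) |

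Over all 12 rows, mid-P agrees within 0.01 in 11. The exception is the 18-case row: its printed rate of 1.19 fits 16 cases, for which mid-P gives 1.19 (0.70-1.88). Exact Poisson does not reproduce the table. Table 6 was therefore built on events per person-year.

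**2. What Kaplan-Meier would return.** Under a constant rate r per 100 person-years, cumulative incidence at t years is 1 − exp(−r·t/100).

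| Rate per 100 person-years | 1 year | 1.5 years | month 25 |
|---|---|---|---|
| 0.59 | 0.59% | 0.88% | 1.22% |
| 0.89 | 0.89% | 1.33% | 1.84% |
| 1.19 | 1.18% | 1.77% | 2.45% |

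The number agrees with the rate at 1 year, is about 1.5 times as large at 1.5 years (1.33 / 0.89) and about twice as large at month 25 (1.84 / 0.89).

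**3. The overall hazard ratio.** The interval is HR × exp(± 1.96·√(1/a + 1/b)) for a and b cases. With the same-size comparator, 8 vs 24 gives 0.33 (0.15-0.74), 12 vs 30 gives 0.40 (0.20-0.78) and 18 vs 36 gives 0.50 (0.28-0.88). The overall comparison is workable.

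**4. Separate hazard ratios by site, if intended.** CAB-LA cases per site: 8/6 = 1.3, 12/6 = 2.0, 18/6 = 3.0. For 12 vs 30 in total, an average site has 2 vs 5, so √(1/2 + 1/5) = 0.837, exp(1.96 × 0.837) ≈ 5.2, and the interval around 0.40 is 0.08-2.06. For 8 vs 24 it is 0.05-2.37, and for 18 vs 36 it is 0.13-2.00. A comparator three times larger hardly helps: 12 vs 78 gives 0.10-2.05.

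The chance that at least one of six equal sites has no CAB-LA case among c is Σ (−1)^(k+1)·C(6,k)·((6−k)/6)^c for k = 1 to 5. This is 89% for c = 8, 56% for 12, 30% for 16 and 22% for 18. The expected number of such sites, 6 × (5/6)^c, is 1.4 for c = 8 and 0.23 for c = 18.

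**The case against.** The best defence is that the intended scale is obvious. The sentence itself asks for a rate, every incidence figure around it is per 100 person-years, and nobody says that a 25-month probability will be reported as an annual rate. With events this rare the two scales agree at 1 year, and Table 5 schedules an analysis after 12 months. This limits the harm but does not remove the error. Table 5 also schedules an analysis at study completion, no time point is attached to Kaplan-Meier, and a 1-year estimate would ignore second-year infections that the 1350 person-years are meant to capture.

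On sites, the defence is that the article does not say whether by site means separate models, interaction terms or stratification. It claims no power within sites, and wide subgroup intervals are a limitation and not a mistake. This stands. If stratification or adjustment is meant, the site point falls away.

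Three stronger readings are tempting, and the documents do not support them:

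- **That the primary-outcome methods as a whole do not suit the data.** The overall Cox hazard ratio has at least 32 events in the Table 6 pairs and matches the detectable ratios, which are relative measures.
- **That site hazard ratios cannot be estimated.** Only a site with no events in one group lacks a finite interval by standard methods. With 18 cases, all six sites have a CAB-LA event with about 78% probability.
- **That the overall model leaves site out.** The article lists no covariates or strata, and a condensed article may leave these to the full protocol or analysis plan.

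**Conclusion.** The analysis sentence is wrong as written: the named estimator does not produce a rate per person-time, which is the quantity the sentence asks for and on which the benchmark, precision statements and Table 6 rest. The gap is nil at 1 year, about 1.5-fold at 1.5 years and about 2-fold at month 25, assuming a constant hazard. It affects the per-group incidence figures, not the overall hazard ratio. The conclusion does not depend on the inconsistent 18-case row.

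The site point is secondary and conditional. If separate site hazard ratios are meant, their limits would be about 16- to 50-fold apart with the same-size comparator (for example 2.00 / 0.13 at 18 vs 36 cases, 2.37 / 0.05 at 8 vs 24). Some would probably not be estimable at 8 or 12 CAB-LA cases. These figures assume equal sites; uneven incidence would make a site without events more likely.

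**What to change.** Restate the estimator: HIV incidence in each cohort is the number of infections divided by person-years, with a mid-P Poisson 95% CI, the method that fits Table 6. Keep Kaplan-Meier for cumulative incidence, labelled as such and reported at a stated time. Leave the overall Cox hazard ratio as it is.

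State what by site means. If separate hazard ratios were intended, report site-specific rates descriptively with their intervals instead.

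The cost is a change of wording. No data collection or sample size changes, and the only loss is a set of site-specific hazard ratios that would say little.

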Owing to user adherence challenges, PrEP has not decreased HIV incidence among some population, particularly among populations with higher susceptibility (youth, racial and ethnic minorities, and TGW) [17-20]. Although HIV incidence in the ImPrEP study population was relatively low (0.85/100 person-years), it was higher among TGW, participants from Peru, those aged 18 to 30 years, Black or mixed-race participants, and those who were nonadherent to daily oral PrEP [15,16]. These disproportionately worse outcomes reinforce the potential of PrEP agents that do not require daily or planned oral dosing to increase their effective use among the most susceptible populations.

In multiple studies, reasons for discontinuing or never initiating daily oral PrEP include low HIV perceived risk, concerns about medication side effects, desire not to take a daily pill, stigma, competing life events, and challenges accessing the medication [13,21-23]. Long-acting PrEP agents may potentially address some of these concerns by providing consistent protection through infrequent, discrete administration, avoiding the need for daily adherence to an oral regimen and the related need for disclosure to sex partners and acquaintances [24].

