Although it is reassuring that CAB-LA has demonstrated comparable effectiveness among youth, Black MSM, and TGW in large clinical trials, the advantages of bypassing daily adherence behavior may not be realized if individuals cannot access injectable PrEP or do not return for repeat injections. Implementation studies are needed to provide crucial information about how interventions that are proven efficacious under randomized clinical trial conditions can be optimized for delivery within real-world service settings. The ImPrEP CAB Brasil implementation study aims to generate critical evidence to inform national policies and program implementers about how injectable CAB-LA PrEP can be provided to MSM, nonbinary persons, and transgender persons within public health PrEP services in Brazil. Its implementation objectives are to describe the facilitators of and barriers to integrating CAB-LA into routine public health clinics and to evaluate whether a mobile health (mHealth) intervention optimizes decision-making on the best PrEP regimen among PrEP users and WhatsApp text messaging improves the uptake of and adherence to CAB-LA injection appointments. The primary clinical objective is to evaluate the effectiveness of CAB-LA PrEP in reducing the risk of HIV acquisition in a study cohort of participants in a context where participants can exercise choice in their HIV prevention method (injectable CAB-LA PrEP or daily oral PrEP).

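### The primary CAB-LA versus oral PrEP hazard ratio compares self-selected CAB-LA users with an external, undefined oral PrEP cohort, with no stated control of confounding and an intent-to-treat label that no randomisation supports

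*Protocol article*

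**What the plan says.** The article's Statistical Analysis section opens with "Our major clinical outcome (primary analysis) will adopt an intent-to-treat approach". It sets HIV incidence in the CAB-LA cohort against incidence "among individuals on daily PrEP within the Brazilian SUS". The model follows: "We will use a Cox proportional hazard model to assess the relative hazard (hazard ratio with 95% CI) between the 2 groups", to be reported "overall and by site, age category, and gender". No covariate, weight, matching rule or comparator restriction is named there. The Abstract adds one word on comparability: "HIV incidence in the CAB-LA cohort (n=1200) will be compared with that in a similar oral PrEP cohort from the public health system".

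Other sections fix how people reach the CAB-LA group. The primary clinical objective, in the introduction's section on injectable cabotegravir, is effectiveness "in a context where participants can exercise choice in their HIV prevention method". Under PrEP Choice and Administration, step 1 participants who prefer oral PrEP go to the routine service and are not actively followed, so they are not a study-run comparison arm. The one randomisation, under Randomized Injection Reminders via WhatsApp, allocates reminders 1:1 among people already enrolled for CAB-LA. Eligibility Criteria limits participants to those aged 18 to 30, in listed gender groups and PrEP naive; undetectable HIV RNA at entry is asked only of those choosing CAB-LA. A further section lets step 1 participants move once from oral PrEP to CAB-LA.

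**The concern.** The objective is causal: whether CAB-LA lowers the risk of acquiring HIV. The contrast chosen to answer it is observational, between people who opted for an injection in six cities and people who take oral PrEP in a national programme. Any factor that differs between the two groups and also affects HIV risk enters the hazard ratio.

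The article itself points to such factors. On incidence in the earlier oral PrEP implementation study, Background says "it was higher among TGW, participants from Peru, those aged 18 to 30 years, Black or mixed-race participants". Entry RNA screening is a second route. If public-system users start without it, early infections already present at their start could be counted as incident in the oral group only.

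The intent-to-treat label makes this harder to see. In a randomised trial it preserves the comparability that randomisation creates; here there is none to preserve for this contrast. The label also fits poorly with a comparator described as people on daily PrEP, which may mean current users rather than everyone who started. Background reports oral discontinuation of about 40% in MSM and over 50% in transgender women, so that distinction matters. The result is meant to inform national policy, and its confidence interval would reflect sampling error alone.

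**Working it through.** **1. What is stated for each group**

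| Feature | CAB-LA cohort | Oral PrEP comparator |
|---|---|---|
| Route into group | Participant's choice | Use of oral PrEP in the public system |
| Age | 18 to 30 | Not stated |
| Prior PrEP | Naive at study entry | Not stated |
| Place | Six named cities | Public system; site implied only by the by-site hazard ratios |
| HIV RNA at entry | Must be undetectable | Not stated |
| Time zero, calendar window | Follow-up from step 2 enrolment | Not stated |
| Oral-to-CAB-LA switchers | May enter step 2 | Not stated whether or when they leave this group |

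Separate hazard ratios by site, age category and gender are estimates within subgroups. They leave the overall hazard ratio as it was.

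**2. The plan's own figures**

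Person-years: 1200 × 1.5 × 0.75 = 1350, as stated.

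Detectable ratios: rate ratio r = (b/T_b)/(a/1350), with 95% limits r × exp(±1.96 × √(1/a + 1/b)). Here a is CAB-LA cases, b comparator cases and T_b comparator person-years. The third CAB-LA row of Table 6 prints 18 cases beside a rate of 1.19. Since 16/1350 = 1.185 and 18/1350 = 1.33 per 100 person-years, 16 is used here; that mismatch is a separate matter.

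- Equal size: 30 v 12 gives 2.50 (1.28 to 4.88); 36 v 16 gives 2.25 (1.25 to 4.06). This reproduces the stated 2.2 to 2.5.
- Three times larger: 78 v 12 gives 2.17 (1.18 to 3.98); 94 v 16 gives 1.96 (1.15 to 3.33). This reproduces the stated 2 to 2.2.

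These figures allow for sampling error only.

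**3. Smallest ratio that would just reach significance**

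Solve ln r = 1.96 × √(1/a + 1/(a·r·k)), where k is comparator size relative to CAB-LA. Two-sided 5% is assumed from the 95% intervals.

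| CAB-LA cases | k = 1 | k = 3 |
|---|---|---|
| 8 | 2.29 | 2.11 |
| 12 | 2.00 | 1.85 |
| 16 | 1.84 | 1.71 |

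The range is roughly 1.7 to 2.3.

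**4. Illustrative bias (all inputs assumed)**

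For one binary risk factor with hazard ratio H and prevalences p₁ and p₀ in the two groups, the bias factor is (1 + p₁(H − 1))/(1 + p₀(H − 1)).

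- H = 2, 50% v 25%: 1.50/1.25 = 1.20.
- H = 3, 60% v 30%: 2.20/1.60 = 1.375.

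If the bias runs in CAB-LA's favour, divide the lower limits from step 2 by it:

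| Scenario | Lower limit | ÷ 1.20 | ÷ 1.375 |
|---|---|---|---|
| 30 v 12, equal size | 1.28 | 1.07 | 0.93 |
| 36 v 16, equal size | 1.25 | 1.04 | 0.91 |
| 78 v 12, three times | 1.18 | 0.98 | 0.86 |
| 94 v 16, three times | 1.15 | 0.96 | 0.84 |

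**5. False significance when the true hazard ratio is 1**

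Poisson simulation with 8 to 16 expected CAB-LA cases, and a comparator of 1350 or 4050 person-years:

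| Assumed bias factor | Nominal 5% test significant |
|---|---|
| 1.0 | 3.5% to 4.6% |
| 1.25 | about 6% to 10% |
| 1.5 | about 13% to 29% |
| 2.0 | about 35% to 78% |

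The high rates need a bias factor of 2.0, well beyond the illustration in step 4.

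**The case against.** The strongest reply is that this is a condensed journal article. Covariate sets, weights and extraction rules commonly sit in a full protocol or analysis plan, which is not shown. A reader might infer that the Cox model is definitely unadjusted. The text does not say so; it says only that two groups are compared and lists no covariates. That part of the reply stands, and the supportable statement is that no control of confounding is stated.

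A reader might also infer an unrestricted, all-ages comparator. The Abstract's word similar, the by-site hazard ratios and the fact that each study site provides public-system PrEP all point towards something comparable. What remains is that similarity is not defined.

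It can also be said that intent-to-treat has a workable meaning in a cohort: analyse by method started, whatever happens later. That is a sensible rule, but the article does not state it, and the comparator's description as people on daily PrEP does not clearly fit it.

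Finally, the bias inputs are assumptions. Background says incidence was higher in certain groups and gives no effect sizes, so it does not show that these are strong determinants. At a bias factor of 1.25 the rise in false significance is modest. Both points stand and limit what can be claimed about size.

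The reply does not remove the main point: what the article does fix is a non-randomised contrast under a label borrowed from randomised trials.

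**Conclusion.** The point holds: as stated, the primary hazard ratio is open to confounding by factors that the article itself links to HIV incidence, and nothing stated deals with them.

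Its size is not known. Under the assumed single risk factor, bias of 1.20 to 1.38 is smaller than the just-significant ratios of 1.7 to 2.3. It is still enough to take the lower limit below 1 in two of the four planning scenarios at 1.20 and in all four at 1.375. These results rest on assumed prevalences and hazard ratios, a two-sided 5% level, and 16 rather than 18 cases in the third CAB-LA scenario.

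Two stronger readings are not supported. One is that the bias has a known direction. A comparator that included older users could make CAB-LA look worse, missing RNA screening in the comparator could make it look better, and selection by choice could act either way. The other is that nothing in the study is randomised: the WhatsApp reminders are, but that allocation lies within CAB-LA users and plays no part in this contrast.

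**What to change.** 1. **Define the comparator.** Use public-system oral PrEP initiators who meet the CAB-LA cohort's age, gender-group and PrEP-naive criteria, at the same sites or cities and in the same calendar window. Set time zero at first dispensation or first injection.
2. **Settle switchers.** State in which group, and from when, people who move from oral PrEP to CAB-LA count.
3. **Change the primary model.** Use a covariate-adjusted or propensity-weighted Cox model with robust variance, built on baseline variables held in both sources: at least age, gender, site and calendar time, with race and STI or behaviour data if recorded. Keep the unadjusted hazard ratio as a sensitivity analysis. The documents do not show which variables public-system records hold, so this must be checked first.
4. **Replace the label.** Write that participants are analysed by method initiated, regardless of later switching or discontinuation.
5. **State the limitation.** Report whether entry RNA screening applied to the comparator.

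The cost is a covariate extraction, revised analysis wording and some loss of effective comparator size from restriction and weighting. Table 6 already considers comparators two and three times larger, which would offset part of that loss. Participant procedures do not change.
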